**Primary Outcomes**
Work-related stress
Non-confidential behavioral cooperation
Confidential behavioral cooperation
**Secondary Outcomes**
Social closeness
Friendship closeness
Sense of belonging

#### Social closeness

Social closeness will be measured using the Inclusion of Other in Self Scale (IOS) [60, 61]. This scale is made up of seven Venn diagram-like pictures where one circle represents the participant and the other circle represents the entire intervention group. The diagrams, ranging from no overlap to near complete overlap, measure close relationships between self and the group by capturing aspects of both feeling close and behaving close. The scale has high reliability for the friendship subgroup sample (Cronbach’s alpha .92) and a high test-retest correlation (r = .86 (n = 31)). Significant correlations between the IOS and measures of closeness that are primarily verbal and multi-item were found (60).

#### Friendship closeness

Friendship closeness will be measured using the Hebrew adaptation of the Friendship Closeness Inventory [41]. The FCI is composed of 49 items that measure closeness in same-sex friendships and is divided into three distinguishable yet related subscales: Emotional Closeness (EC), Behavioral Closeness (BC), and Cognitive Closeness (CC). For the purposes of the present study the first item will be adjusted to include a reference to participants in the intervention group alone: “*Do you have friends among the participants in the physical training group whom you consider to be ’close friends’*?”. The scale has high reliability for both the total score (Cronbach’s alpha .94) and for the subscales scores (Cronbach’s alpha .91 for EC, Cronbach’s alpha .93 for BC and Cronbach’s alpha .87 for CC) [41].

#### Sense of belonging

Sense of belonging will be measured using the Hebrew adaptation of the General Sense of Belonging Scale [62]. This scale is composed of 12 items that measure sense of belonging (achieved belongingness) which are rated on a 7-point Likert scale ranging from “Strongly Disagree” (1) to “Strongly Agree” (7). Six items measure sense of acceptance and inclusion; for example: *I have a sense of belonging*. The other six items measure sense of rejection and exclusion; for example: *I feel like an outsider*. For the purposes of the present study, the scale will be adjusted so that the words “other people” or “others” will be replaced by the words “participants in the physical training group”; for example: “*When I am with participants in the physical training group*, *I feel included*”. The scale has high reliability (Coefficient alpha = .94 and an average inter-item correlation (AIC) = .57 (M = 66.3, SD = 13.5) and strong patterns of validity estimates have been established (62). The original version of the General Sense of Belonging Scale [62] will also be used to validate the adapted one.

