### Quantitative data collection: Outcome variables

Quantitative data on the following outcome variables (as listed in Table 2) will be collected for each participant using validated questionnaires and behavioral tasks at three points of time: before the first intervention session, after the last intervention session (pre-post) and 17 weeks after the end of the intervention period (follow-up). The data collection procedure will be administered by the first author in a group session, corresponding to the same group as the intervention group, in a classroom at RRP facilities. This procedure will be composed of two parts: (a) A group behavioral task which will be recorded using one video camera. (b) Questionnaire administration via online software (Qualtrics).

**Table 2 pone.0307956.t002:** Study outcomes.

Outcomes

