#### Quantitative data analysis

The data obtained as study variables will be coded, processed and analyzed at the end of the collection process. IBM SPSS Statistics Version 27 will be used for statistical analysis. To control the family-wise error rate when performing multiple hypothesis tests, Bonferroni Step-Down (Holm) procedure will be applied. Participants must attend at least 4 sessions to be included in the analyses. To describe the sample, descriptive statistics will be calculated followed by univariate and bivariate statistical analyses. The first step will be to assess whether the data follows a normal distribution for each of the variables which will guide the choice of parametric or non-parametric tests. To answer the primary study objective and the first secondary study objective, the effects of the intervention over time (at the end of the intervention and after 17 weeks) will be examined using a two-way mixed model ANOVA. To explore the second secondary study objective, the influence of the need to belong on the effect of the intervention over time (at the end of the intervention and after 17 weeks) will be examined using a three-way mixed model ANOVA.

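### Two secondary scales ask about the training group before it has trained; the arm-by-time ANOVA gives that baseline full weight and may lose precision

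*Protocol article*

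**What the plan says.** All references are to the protocol article.

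- **Referent of the scales.** Under *Social closeness*, the picture scale is one "where one circle represents the participant and the other circle represents the entire intervention group". Under *Sense of belonging*, the general wording is replaced so that the items refer to "participants in the physical training group".
- **Timing.** *Quantitative data collection: Outcome variables* places the three measurements "before the first intervention session, after the last intervention session (pre-post) and 17 weeks after the end of the intervention period (follow-up").
- **Setting.** The same section says data are collected "in a group session, corresponding to the same group as the intervention group, in a classroom at RRP facilities". The first-listed part is "A group behavioral task which will be recorded using one video camera"; the questionnaires are listed second.
- **Analysis.** Under *Quantitative data analysis*, the effect over time for the primary objective and the first secondary objective (closeness and belonging) "will be examined using a two-way mixed model ANOVA". *Sample size* describes three measurements.
- **Unadapted belonging scale.** It "will also be used to validate the adapted one". No time point is given for it.

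For the friendship inventory, only the first item is said to be tied to the intervention group, so it is left out of this point.

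**The concern.** Before session 1, a question about closeness to, or inclusion in, the training group is answered on expectation and brief contact. Afterwards it is answered on ten weeks of shared sessions. The wording is the same, but what it captures may differ, so the baseline may carry little information about the later scores.

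An arm-by-time interaction over three times does not let the data decide how much weight that baseline deserves. It works on within-person contrasts, so baseline enters with a fixed coefficient. If baseline is as variable as later scores but weakly related to them, subtracting it adds noise. With about 30 per arm before dropout, and Holm adjustment on top, a real difference in closeness or belonging could be missed for a reason that analysis wording can avoid.

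**Working it through.** **1. The plan's own figure.** Inputs from *Sample size*: f = 0.25, 80% power, alpha 0.05, four groups, three measurements, N = 40. The article states neither the correlation among measurements nor the sphericity correction; I assume 0.5 and 1.

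- lambda = f² × N × m / (1 − rho) = 0.0625 × 40 × 3 / 0.5 = 15
- df1 = (4 − 1)(3 − 1) = 6; df2 = (40 − 4)(3 − 1) = 72
- Power = 0.805, so N = 40 is reproduced.

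For the two-arm interaction actually planned, at N = 60 and the same f, power is 0.92 at a common correlation of 0.2 and 0.85 at 0. On the plan's own effect size, a weak correlation alone does not take power below 80%. That effect is large, however. With equal effects d at both later times and none at baseline, f = d/√18, so f = 0.25 means d = 0.25 × 4.243 = 1.06. I therefore also look at d = 0.5, which is an assumption.

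**2. One later time, equal SDs.** Let rho be the baseline-to-post correlation. Relative variance of the arm difference:

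- change score: 2(1 − rho)
- post score alone: 1
- ANCOVA on own baseline: 1 − rho²

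Change is worse than post alone when 2(1 − rho) > 1, that is, when rho < 0.5. Change minus ANCOVA is 2(1 − rho) − (1 − rho²) = (1 − rho)², which is never negative.

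Power by noncentral t, 30 per arm, d = 0.5:

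| rho | Change | Post alone | ANCOVA |
|---|---|---|---|
| 0 | 0.270 | 0.478 | 0.478 |
| 0.2 | 0.325 | 0.478 | 0.493 |
| 0.5 | 0.478 | 0.478 | 0.594 |
| 0.7 | 0.691 | 0.478 | 0.760 |

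**3. The planned three-time test.** Simulation with 30 per arm, d = 0.5 at both later times, correlation 0.6 between them, equal SDs, Greenhouse-Geisser correction, two-sided 5%, no Holm adjustment and no clustering:

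| Baseline correlation | Arm-by-time test | ANCOVA on post |
|---|---|---|
| 0 | 0.27 | 0.45 |
| 0.2 | 0.33 | 0.49 |
| 0.5 | 0.50 | 0.58 |
| 0.7 | 0.69 | 0.75 |

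Post scores alone give about 0.46 to 0.48 throughout.

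**4. Allowing for two looks.** The interaction has 2 degrees of freedom and the ANCOVA above tests one time. A fairer comparison runs ANCOVA at both later times and applies Holm to the pair, so that at least one is declared if the smaller p-value is below 0.025. In 20,000 simulated trials under the same assumptions, that happens in about 0.50, 0.52, 0.65 and 0.85 at the four correlations, still above the interaction test at each.

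**5. A floor at baseline.** If the baseline SD is a fraction s of the later SD, the change-score variance is 1 + s² − 2·rho·s. At rho = 0 this is 1.25 for s = 0.5 and 1.09 for s = 0.3, against 2 for equal SDs. Simulated arm-by-time power is then 0.42 (s = 0.5, rho = 0), 0.49 (0.5, 0.2), 0.48 (0.3, 0) and 0.52 (0.3, 0.2). Against about 0.48 for post alone, the loss is at most about 5 to 6 points.

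**The case against.** The strongest reply is that the baseline is not empty. The baseline session is run in the intervention group, with a group task listed before the questionnaires, and members come from one program cycle and share a 13-week course. They may well have views about these people that persist. The article gives no correlation; at 0.5 the interaction test does as well as post scores alone, and at 0.7 it does clearly better. This stands, and it makes the loss conditional. It does not rescue the choice of model, because ANCOVA had the higher power at every correlation tried.

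Four stronger readings are tempting and are not supported:

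- *The group has not met at baseline.* The text supports only that it has not yet trained together.
- *The baseline is a guess or a floor score that wrecks the test.* Neither is shown, and a floor with little spread largely removes the loss.
- *The arm comparison is biased.* Under randomisation, a weak baseline adds noise in both arms alike.
- *The unadapted belonging scale is already available as a better baseline.* It is collected to validate the adapted one, with no stated time point.

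Averaging the two later scores looks stronger still (about 0.57), but that assumes an equal effect at 17 weeks. The article's introduction cites a workplace study whose effects on stress and sick days were not seen after three months.

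It may also be said that covariates belong in an analysis plan. True, but here the article itself names the model.

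**Conclusion.** The point holds as a conditional loss of precision on two secondary outcomes. With equal spread and a baseline correlation of 0 to 0.2, the planned test has about 0.27 to 0.33 power where ANCOVA on the post score has about 0.45 to 0.49, a gap of 16 to 18 points. At 0.5 to 0.7 the gap is 6 to 8 points. These figures rest on an assumed d = 0.5 at both later times, 30 completers per arm, correlation 0.6 between those times, and no clustering. The primary outcomes, the stated sample size and the validity of the randomised comparison are not affected.

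**What to change.** For the closeness picture scale and the adapted belonging scale only:

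- Compare arms on the post score and on the 17-week score by ANCOVA, or with a longitudinal model of those two times.
- Use as covariates the scale's own baseline and the continuous need-to-belong score, which *Study design* collects before allocation. Add the unadapted belonging scale if it is in fact given at baseline.
- Do not test these scales through the arm-by-time interaction with baseline as a time level. Report within-person change descriptively.
- Keep the scale's own baseline: as a covariate it costs almost nothing when uninformative (0.453 against 0.461 for post scores at correlation 0) and gains as the correlation rises.

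The cost is analysis wording and no new data. Change from baseline is no longer the tested quantity, and each covariate uses one degree of freedom. The article says analysis follows the end of data collection and that the fourth cycle was still running, so on that account the change could be fixed before the data are analysed.

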#### Work-related stress

Work-related stress will be measured using the Hebrew adaptation of the Irritation Scale [63]. This scale comprises eight items, three of which assess cognitive irritation and five of which assess emotional irritation. Items are rated on a 7-point Likert scale ranging from “Strongly Disagree” (1) to “Strongly Agree” (7). For the purposes of the present study, the scale will be slightly adjusted in that the words “at work” will be replaced by the words “in the course”, for example: “*Even at home I often think of my problems in the course*”. The scale has high reliability (Cronbach’s alpha .89) and for the German version, a large number of studies report correlations between this scale and stressors at work, further impairments such as psychosomatic complaints or depression, and missing resources such as social support [63].

#### Prosociality

Prosociality will be measured using the following behavioral group cooperation tasks, both of which resemble the classic N-person cooperation dilemma as a “collective action problem of a common good” as described by [64].

*1*. *Collection task*. Participants will have to work together to pick up 100 small washers (a flat plastic coin with a diameter of 4 cm), as described in [65]. The participants will be asked to remain quietly in their seats for 5 minutes while the washers are being randomly scattered in a rectangular structure on one side of the classroom. Then the participants will be asked to pick up one washer at a time and put it in a small basket located on the other side of the classroom in the shortest time, until all washers are collected by the group. Only then will they be able to return to their seats and remain quietly for another 5 minutes. Participant will be asked to abstain from running to avoid collisions and maintain group safety. In this specific task, the act of gathering washers embodies the concept of the common good. Participants must collect all washers and place them in a small basket before returning to their seats. However, the temptation to free ride, relying on others’ efforts, illustrates the collective action problem. While it benefits both individuals and the group to gather the washers, the impact of any single person’s contribution is minimal and difficult to discern. This dynamic creates an incentive to conserve energy by abstaining from action and allowing others to undertake the task. Participants must work together toward a common goal (collecting all washers in the shortest time), therefore there is likely no incentive to compete. As in previous social loafing paradigms [66], cooperation on this task will be operationalized by participants’ effort to overcome the incentive to conserve energy, represented by their step rate (number of steps per second). The number of steps will be measured using a wearable fitness tracker (Fitbit Inspire 2) that will be attached to the participants’ wrists using a special band. Fitbit fitness trackers are commonly used in clinical trials [67]. Each tracker will be customized with participants’ personal height and weight to ensure step rate accuracy. The collection procedure will be recorded using one video camera to control task execution. Since cooperation on this task will depend on the participants’ physical fitness and might be influenced by group pressure, we will also use a non-physical confidential task to measure pure voluntary cooperation.

*2*. *Public goods game*. Participants will be told they will be given 30 NIS and that they can donate some or all of it to a group investment, as described in [68]. The money in the group investment will then be doubled and divided equally among all members of the group. The money earned in this game will be compensation for participating in the study. In contrast to the collection task, participants’ contribution will be confidential to avoid group pressure. Cooperation on this task will be operationalized by the amount of money each participant decides to donate to the group investment.

### Qualitative data collection

Qualitative data will be collected from the participants till data saturation is achieved, using semi-structured interviews. After each intervention cycle, all participants will be asked to volunteer to be interviewed. The interviewees will be chosen out of the pool of volunteers based on the following criteria: (a) At least one participant from each intervention group. (b) At least one participant from each army related profession. (c) High verbal self-expression—the participant must have been appraised by army officers as being able to verbally express thoughts, emotions and views. The interviews will be carried out one to two weeks after the end of the intervention cycle. The interview guide for the semi-structured interviews will be composed of 11 questions ranging from the most general (e.g., “*How did you experience the course in general*?”) to the most specific (e.g., “*How did the group physical training sessions affect your experience during the course*: *(a) with respect to your sense of belonging (b) with respect to friendship closeness (c) with respect to your sense of involvement and cooperation (d) with respect to your work-related stress*”). In order to merge the qualitative and quantitative data, the qualitative questions in the interview guide will be congruent with the quantitative objectives of this study. To motivate the participants to discuss their perspective and express their emotions, two questions out of the 11 will be administered using a set of projective cards. This set of cards contains 13 words and 17 pictures reflecting associations with the word “group”. On the first question the participants will be asked to choose a word that best describes their relationship with other members of the intervention group (e.g. “coherence”, “loneliness” and “opportunity”) and to explain why they chose this specific word. On the second question the participants will be asked to choose the picture that best depicts their experience during the group intervention process and to explain why they chose this specific picture. The use of semi‐ambiguous words and pictures is less challenging for individuals on the autistic spectrum than the presentation of more ambiguous stimuli. The interviews will be conducted by the first author and will be audio recorded and fully transcribed before analysis.

### Data analyses

To answer the five study objectives (see above in Introduction) the following data analysis will be conducted:

#### Quantitative data analysis

The data obtained as study variables will be coded, processed and analyzed at the end of the collection process. IBM SPSS Statistics Version 27 will be used for statistical analysis. To control the family-wise error rate when performing multiple hypothesis tests, Bonferroni Step-Down (Holm) procedure will be applied. Participants must attend at least 4 sessions to be included in the analyses. To describe the sample, descriptive statistics will be calculated followed by univariate and bivariate statistical analyses. The first step will be to assess whether the data follows a normal distribution for each of the variables which will guide the choice of parametric or non-parametric tests. To answer the primary study objective and the first secondary study objective, the effects of the intervention over time (at the end of the intervention and after 17 weeks) will be examined using a two-way mixed model ANOVA. To explore the second secondary study objective, the influence of the need to belong on the effect of the intervention over time (at the end of the intervention and after 17 weeks) will be examined using a three-way mixed model ANOVA.

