A new wave of research in autism suggests that in addition to difficulties with social interactions and stressful environments, ASD is also characterized by fundamental differences in sensorimotor functioning including the delayed development of motor skills [7], abnormal gait [8], difficulty with balance [9], difficulties in coordinating movements that involve both sides of the body, and in controlling force and direction when throwing a ball [10]. These altered modes of perceiving and moving in the world (alone, as well as with other people) may help explain some of the key fundamental social impairments in autism and asynchronous social behavior in particular [11–15]. Asynchronous social behavior in autism (e.g., reduced eye contact, absence of well-timed co-regulation, no coherent engagement of mutual attention, no anticipation and no emotional build up in shared interactions) was first identified in a micro-analytic study of videos of an 11-month old infant who was diagnosed with ASD during her second year of life [16]. Stronger evidence for the association between atypical interpersonal synchrony and autism was recently described [13] in a study which also suggested that there may be a disruption in intrapersonal mechanisms such as atypical motor timing, and in interpersonal mechanisms such as atypical inter-individual coupling.

The aim of this trial is to assess the effects of group interpersonal synchrony on the prosociality and work-related stress of young autistic adults in their work environment. The trial is designed as a randomized controlled trial with two parallel groups (experimental group and treated control group), primary and secondary endpoints and a follow-up of intervention effectiveness after 17 weeks as described in Fig 1. Randomization will be performed as block randomization with a 1:1 allocation. In the following sections we review research on interpersonal synchrony in autism and on the associations between interpersonal synchrony, prosociality and work-related stress.

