### Sample size

A meta-analysis on prosocial consequences of interpersonal synchrony among neurotypical adults found a medium-sized effect of interpersonal synchrony on prosociality with regard to both attitudes and behavior towards individuals or groups involved in the same intervention [28]. Therefore, an effect defined as d = 0.25 may be expected [49]. An a-priori power analysis using the G*Power computer program [50] indicated that a total sample size of 40 participants would be needed to detect medium-sized effects defined as f = 0.25, with 80% power and alpha at .05, using a repeated measure, within-between interaction ANOVA with four groups and three measurements. We will recruit at least N = 60 participants (30 in each intervention group) to plan for possible dropouts.

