### Study design

This study will implement a randomized controlled trial (RCT) design to investigate a synchronous or non-synchronous movement-based group intervention, so that each participant will only engage in one intervention condition, alongside a phenomenological study with the participants of both groups. The RCT will compare the experimental group (synchronous movement) with a treated control group (non-synchronous movement) and will follow the recommendations of the Consolidate Standards of Reporting Trials (CONSORT) [51] and the recommendations of the Standards for Reporting Qualitative Research [52]. In addition, the SPIRIT guidelines [53] have been followed. Fig 1 outlines when each study component occurs. This design does not include a nontreated control group to meet the program’s requirement that all trainees should participate in all course activities including the movement-based group intervention. The study was registered with ClinicalTrials.gov (registration number: NCT05846308) afterthe enrolment of participants started due to the uncertainty about the clinical character of the target population and intervention. The authors confirm that all ongoing and related trials for this intervention are registered.

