The condition groups will be matched according to the following control variables: (a) gender (male/female); since there is diagnostic gender bias with respect to ASD [54] (b) army related profession (image interpretation/GIS/data analytics/software programming/electro-optics/data annotation) (c) handedness (right-handed/left-handed); since there is a larger distribution of left-handedness in the ASD population compared to the general population [55] (d) need to belong level (NTBL) (high/low). To control for handedness and NTBL during the randomization process, the following questionnaires will be administered to the participants: (a) The Hebrew adaptation of the Edinburgh Handedness questionnaire [56], the most common method for measuring handedness in individuals with Autism [57]. (b) The Hebrew adaptation of the Need to Belong (NTB) Scale [59] which comprises ten items rated on a 5-point Likert scale ranging from “Strongly Disagree” (1) to “Strongly Agree” (5). This scale has acceptable interitem reliability (the Cronbach’s alpha generally exceeds .80) and has been positively correlated with extraversion, agreeableness, and neuroticism and with having an identity that is defined in terms of social attributes [58]. NTBL(high/low) will be calculated using a cut-off of the NTB measure, so that participants with the 50% highest NTB score will be assigned a high NTBL and the rest will be assigned a low NTBL. After inclusion in the study and assessment of the control variables, participants will be assigned by the first author to one of the intervention conditions on an individual basis according to a computer-generated randomization procedure. The allocation ratio of the intended numbers of participants in the comparison groups will be 1:1 so that the number of participants assigned to the synchronous intervention will be similar to the number of participants assigned to the non-synchronous intervention. To this end, we will first create subgroups containing participants with same gender, army-related profession, handedness and NTBL. For each subgroup, alternate assignments will be made in random order. The order of subgroup assignments will also be determined randomly. For the first subgroup, we will use a simple coin flip randomization procedure to determine the intervention type to start assigning to. An overview of the study design is shown in Fig 3.

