### Procedure

The interventions will be conducted by the first author, who is a professional Dance Movement therapist, as part of the RRP course, once a week for the duration of the 10 weeks of each program cycle. A graduate student of the RRP will take part as a co-instructor for modelling and assistance. Each intervention group will have between 10 and 14 participants. Since autistic participants may feel anxious without a predictable structure, a structured physical training protocol will be used for each condition. The protocols were designed by the first author with the help of a professional physical trainer and after consulting with dance movement therapists who have research experience in the area of synchrony interventions in ASD. Each protocol is composed of 10 physical training sessions, each lasting 60 minutes. The protocols differ in terms of using synchronous activity vs. non-synchronous activity. They do not differ in terms of physical exercise type or duration to control for the effect of exercise type and duration on the dependent variables. Some exercises include the use of a training mattress, an elastic band or a sponge ball. To allow for some flexibility in terms of spontaneous synchrony, each session includes a social engagement segment either as a warm-up or as a social game. A Tabata Timer [59] will be used to break the workout into clearly defined intervals during the main training segment. A metronome beat (every second) will be used to help the participants do the exercises at the right pace.

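### The only stated quantitative analysis set leaves out randomised participants who attended fewer than 4 of 10 sessions, so it is no longer the randomised set

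*Protocol article*

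**What the plan says.** The Introduction states "Randomization will be performed as block randomization with a 1:1 allocation". The Study design section places allocation at entry: "After inclusion in the study and assessment of the control variables, participants will be assigned by the first author to one of the intervention conditions", individually and by a computer-generated procedure. The Procedure section sets the exposure: "Each protocol is composed of 10 physical training sessions, each lasting 60 minutes", delivered weekly.

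Outcome measurement carries no attendance condition. The section on outcome variables says "Quantitative data on the following outcome variables (as listed in Table 2) will be collected for each participant" at three time points: before the first session, after the last, and 17 weeks later.

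The Quantitative data analysis section then states "Participants must attend at least 4 sessions to be included in the analyses". The sentence comes before the descriptive, primary and secondary quantitative analyses and exempts none of them. It is not labelled per-protocol or sensitivity, and the article states no analysis of all participants as allocated.

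**The concern.** Allocation is fixed before any session, whereas the number of sessions attended is known only weeks later. A set defined by attendance is therefore selected on behaviour that the allocated condition can influence. The article itself makes this plausible. The synchronous arm exercises in a circle facing one another. The control arm uses stations set up so that participants do not face each other. The background cites a study in which autistic adults were less inclined to continue a synchrony game. That does not show which arm would lose more people, only that tolerance of the task may matter.

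The outcomes are work-related stress, cooperation, closeness and belonging. Reasons for staying away could overlap with these. If so, the included participants in the two arms would differ for reasons other than the intervention, and randomisation would no longer protect the primary comparison. The balancing on gender, profession, handedness and need to belong could also be disturbed.

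**Working it through.** **1. Timing.** Sessions are weekly, so nobody can meet the threshold before the fourth session. Allocation precedes the first. Membership of the analysis set is therefore a post-randomisation variable.

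**2. The plan's own figure.** The Sample size section says a total of 40 "would be needed to detect medium-sized effects defined as f = 0.25", "with 80% power and alpha at .05", for a within-between interaction with four groups and three measurements. Using λ = f²·N·m/(1−ρ), df1 = (k−1)(m−1) and df2 = (N−k)(m−1), with k = 4, m = 3 and assumed ρ = 0.5 and sphericity:

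- N = 40: λ = 0.0625 × 40 × 3 / 0.5 = 15, df 6 and 72, power 0.805 (N = 36 gives 0.749). The 40 reproduces.
- N = 60: λ = 22.5, power 0.954 (0.991 if k = 2, the number of arms compared).

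The 40 does not depend on the attendance rule. With complete data on all 60, the rule is not needed for power.

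**3. Level or change.** Let low attenders differ from attenders by a constant g at every time point. Excluding a share p shifts the mean of those included by p·g at baseline and by p·g afterwards. The shift in change is p·g − p·g = 0, so a stable gap cancels in the group-by-time interaction. Only a gap in *change* biases that test.

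**4. Bias in change.** Assume no true effect and a mean change of zero in each full arm. Let g be the mean change of attenders minus that of low attenders. From (1−p)·μ_in + p·(μ_in − g) = 0, the included mean is μ_in = p·g. With the same g in both arms, the between-arm bias is (p1 − p2)·g. The article gives neither p nor g, so all values here are assumed:

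| Excluded, arm by arm | g = 0.5 SD | g = 0.8 SD | g = 1.0 SD |
|---|---|---|---|
| 10% and 10% | 0 | 0 | 0 |
| 5% and 20% | 0.15 × 0.5 = 0.075 | 0.15 × 0.8 = 0.12 | 0.15 × 1.0 = 0.15 |
| 0% and 20% | 0.20 × 0.5 = 0.10 | 0.20 × 0.8 = 0.16 | 0.20 × 1.0 = 0.20 |

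With 30 per arm, 5% and 20% are 1.5 and 6 people. The zero in the first row needs the same kind of person to be excluded in both arms. With 10% each but gaps of 0.5 and 1.0 SD, the bias is 0.10 × 1.0 − 0.10 × 0.5 = 0.05 SD.

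**5. Cross-check.** Suppose instead that the lowest share p on a latent attendance variable is dropped, and that this variable correlates r with the outcome. The shift in each arm is r·φ(c)/(1−p), with c = Φ⁻¹(p). For r = 0.3 to 0.5:

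- 5% and 20% excluded: 0.07 to 0.12 SD.
- 0% and 20% excluded: 0.11 to 0.18 SD.
- 10% in each arm: 0.

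A null simulation (30 per arm, r = 0.5, 5,000 runs, t-test at one time point) gave a type I error of 0.072, 0.089 and 0.051 for those three cases. Analysing everyone gave 0.046 to 0.049. The simulation concerns a level at one time point, not the planned interaction. It shows the mechanism and does not estimate this trial's error rate.

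**The case against.** The strongest reply is that few people may be excluded. The host programme expects all trainees to take part, the sessions sit inside the course schedule, and motivation is expected to be high. The threshold is lenient and identical in both arms. This stands as a limit on size, and the bias may be close to zero. It does not justify the rule: if almost nobody falls below four sessions, analysing everyone costs almost nothing.

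It is also right that stable differences between attenders and low attenders cancel in the group-by-time test (step 3). Bias needs a difference in change.

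Some stronger readings are tempting but not supported:

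- A reader might infer that the bias could create or hide an effect of the planned size. The range of 0.08 to 0.15 SD is below even d = 0.25. The Sample size section gives both d = 0.25 and f = 0.25. For two equal groups d = 2f, so f = 0.25 corresponds to d = 0.5. The illustrative 0.12 SD is 0.12/0.25 = 48% of one and 0.12/0.5 = 24% of the other.
- A reader might take 60 recruited for 40 needed as a forecast that a third will be excluded. That margin is for dropouts. Those with no outcome data would be missing under either analysis.
- A reader might extend the rule to the interviews. The sentence stands in the quantitative section, and interviewees have their own selection criteria.

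A separate analysis plan may exist. The point, however, concerns a rule that the article states outright, so it does not rest on a missing detail.

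**Conclusion.** The concern holds in this form: the only stated quantitative analysis set is conditioned on attendance after randomisation, and the comparison of change between arms can be biased as a result. Two conditions are needed. Exclusions must differ between arms in number or kind, and low attenders must change differently from attenders.

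Neither the size nor the direction can be derived from the article. The 0.08 to 0.15 SD rests on three assumptions: 5% and 20% excluded, a gap in change of 0.5 to 1.0 SD, and the same gap in both arms. Such a bias could distort the result. On these figures it would not by itself produce or cancel the planned effect.

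**What to change.** - Define the primary quantitative analysis as all randomised participants in their allocated arm, whatever their attendance.
- Use all available outcome data with a method that handles missing outcomes, for example a likelihood-based mixed model for repeated measures. A conventional mixed ANOVA keeps only participants with all three measurements and would bring back some of the selection.
- Keep the set with at least 4 sessions as a labelled per-protocol sensitivity analysis.
- Report attendance and exclusions by arm.
- Continue to measure low attenders in the cycle still running.

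The change can still be made before analysis, since the article has data analysed at the end of collection and describes the fourth cycle as in process. It is not purely a matter of wording. Three cycles are complete, and any low attenders not measured there cannot be recovered. The article says outcomes are collected for each participant, so this may not arise. The other cost is dilution: if 20% of the synchronous arm gained nothing (assumed), the average effect would be 1 − 0.20 = 0.80 of that in attenders.
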